# Outcomes

The characteristics of the participants will be gathered at baseline before the intervention, including: (1) their sociodemographic data, such as their age, gender, educational attainment, employment, and relationship with each other; and (2) their clinical data, such as patients’ NHYA classification, length of time that they have had the disease, comorbidities and activities of daily living (ADL), and caregivers’ length of caregiving. The effectiveness of the interventions will be evaluated at the dyadic level and individual level for patients and their caregivers at baseline, immediately post-intervention, and at 3 months post-intervention.

All health outcome assessments will be tested using reliable and valid scales. The research assistants have been fully trained in outcome assessments to ensure quality and consistency; they will interview patients with CHF and their FCs to complete the online assessments (http://www.wenjuan.com/) via smartphone in a private office. Participants who discontinue the intervention will be encouraged to participate in the outcome assessments.

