# Eligibility

## Participants of the present study involve both patients with CHF and their corresponding primary FCs. CHF patients will be eligible if they are 18 years of age or older, have been clinically diagnosed with CHF (40) as indicated in their electronic medical records, and with a New York Heart Association (NYHA) Classification of I to III as confirmed by a physician in this study, have been hospitalized in the past one year. CHF patients will be asked to nominate their primary FC, who would be the one with the highest average number of contact hours among their family members, to join the program. FCs should have aided patients with care needs for a minimum of 14 hours per week consistently for at least three months. FCs should be 18 years of age or older, and they can be patients’ spouse, parent, or adult child, but not a paid caregiver or other relative. In addition, at least one member of the patient-caregiver dyad will be required to have a smartphone installed with the WeChat app and a data plan. Both members should understand and communicate in Chinese, as well as be able to access Tencent VooV Meeting via smartphone to attend the sessions.

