## Patients and their FCs will be required to participate in the group sessions on a dyad basis. During the intervention period, if either member has been hospitalized, sessions will be suspended during the period of hospitalization and will resume after she/he is discharged to go home.

# Sample size calculation

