# Interventions

Participating dyads will be allocated to either the intervention group or the control group. All of them will receive four identical weekly sessions via the Tencent VooV meeting over four consecutive weeks in addition to the usual care provided by the department of cardiology. Each session will include four to eight dyads and last approximately two hours, and will be led by a registered nurse(s) with technical support from two research assistants throughout the sessions. Participants will receive relevant materials and handouts prior to the first session, and they will be instructed to retain these materials and handouts throughout the duration of the study and beyond. The online sessions will be scheduled on weekday evenings and weekend afternoons to accommodate typical family events and work schedules. During the period of the interventions, WeChat voice calls or text message reminders will be sent to the dyads before each session to improve participant retention and support engagement in the program.

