**Patient-only outcomes:**

**Health service utilization**

The frequency of all course and cardiac-related readmissions and emergency department visits in any hospital will be assessed by self-reports.

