To promote recruitment and retention, the dyad will be given an incentive to undergo each assessment during the study, as compensation for their time; for example, each participating dyad will receive one set of CHF self-care materials for the baseline assessment, 50 Yuan RMB (≈6.97 USD) for each session, 50 Yuan RMB (≈6.97 USD) for the post-intervention assessments while 100 Yuan RMB (≈ 13.95 USD) for the 3-month follow-up assessment. The monetary incentives will be sent to the family via the WeChat platform. The material will be sent directly to the family by post.

A detailed schedule and timing of the evaluations are presented below in Table 2. T5 and T6 represent the time immediately post-intervention and at the 3-month follow-up point, respectively.

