# Statistical analysis

All quantitative data collected from the participants will be numerical coded, and analyzed utilizing IBM SPSS 27. Baseline sociodemographic and clinical data will be used using medians, proportions, and counts for categorical data; while means, standard deviations (SDs), skewness, and kurtosis will be used for continuous variables for participants in two groups. Differences in the participants’ characteristics at baseline will be explored using an independent T-test or Mann-Whitney U test for continuous variables, and Chi-squared or Fisher’s Exact test for categorical variables. The primary outcome and secondary outcomes will be summarized using means with SDs for the ACT group and CE groups. Randomized testing at baseline between the study groups will be performed to identify potential covariates. The differences in these outcomes between the ACT group and the CE groups over time will be analyzed using generalized estimating equations (GEE) which account for missing data at random. If any covariance is detected in the baseline comparison, it will be adjusted in the analysis of the effects of the intervention. Subgroup analysis will be adopted for specific factors (e.g., intervention completion and non-completion). The level of statistical significance is predetermined at p<0.05 (two-tailed). The intention to treat principle will be applied by comparing the ACT group with CE groups as randomized despite adherence to the intervention. Cohen’s d will be calculated to estimate effect sizes of between-group comparisons.

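### Admission and emergency-visit counts go through the same baseline/post/3-month GEE as the scale scores with no counting period stated, so change from baseline may be uninterpretable and the between-arm contrast less precise than it need be

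*Protocol*

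**What the plan says.** The Outcomes section sets one schedule for evaluating effectiveness: "for patients and their caregivers at baseline, immediately post-intervention, and at 3 months post-intervention". The Statistical analysis section summarises primary and secondary outcomes alike as means with SDs and then states: "The differences in these outcomes between the ACT group and the CE groups over time will be analyzed using generalized estimating equations (GEE". No link, count distribution or exposure term is mentioned.

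Among the secondary outcomes, Health service utilization reads: "The frequency of all course and cardiac-related readmissions and emergency department visits in any hospital will be assessed by self-reports". It gives no recall or counting period, and no index discharge from which a readmission would be reckoned.

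Four other statements bear on the count:
- Eligibility requires that patients "have been hospitalized in the past one year". That clause does not restrict the cause.
- Interventions provides "four identical weekly sessions via the Tencent VooV meeting over four consecutive weeks".
- Eligibility also says that if either member is admitted, "sessions will be suspended during the period of hospitalization and will resume after she/he is discharged to go home".
- Procedure says that "T5 and T6 represent the time immediately post-intervention and at the 3-month follow-up point, respectively", and refers to Table 2 for the detailed schedule. That table is not in the text available for review.

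**The concern.** A scale score describes a state at a visit, so three visits give three comparable values. An event count means nothing without the period over which it is taken. Two natural readings make the three values unlike each other. If each visit asks about events since the last one, the two follow-up counts cover about 4 weeks and 3 months. If the baseline question looks back about a year and includes the admission that qualified the patient, the baseline count has been selected to be non-zero.

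The interval to T5 can also be lengthened by the outcome itself, because an admission postpones the remaining sessions. Exposure may therefore differ between patients.

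At stake are the reading of any within-arm time trend for hospital use and the precision of its group-by-time contrast. Because the data are self-reported, the period is fixed by the interview question. A later analysis plan cannot recover a count over a period that patients were not asked about.

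**Working it through.** **The plan's own figures.** There is none for hospital use. The sample size (d = 0.50, power 0.80, two-sided 0.05) reproduces as 64 per arm, 128 in all, and 128/0.80 = 160. It concerns quality of life and does not bear on this point.

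**Inputs from the protocol.** At least one admission in the prior 12 months; about 4 weeks (1/13 year) to T5; 3 months (1/4 year) from T5 to T6.

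**Assumptions, not in the protocol.** Before selection, each patient has a constant admission rate drawn from a gamma distribution with annual mean m = 0.6 to 1.5 and variance k·m², k = 0.5 to 1. Counts are Poisson and there is no treatment effect. The baseline look-back is u = 12, 3 or 1 months (in years below). The illustration uses m = 1, k = 1.

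**1. Period length.** At a constant rate, the 3-month count is (1/4)/(1/13) = 3.25 times the 4-week count.

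**2. Entry rule.** The chance of no admission in a year is p0 = (1+km)^(−1/k). Let s = 1 − p0.
- Mean 12-month baseline count after selection: m/s = 1/0.5 = 2.00.
- Annual rate afterwards in the same patients: m[1 − (1+km)^(−1−1/k)]/s = (1 − 0.25)/0.5 = 1.5.
- Mean count at T5: 1.5/13 = 0.12. At T6: 1.5/4 = 0.375.
- Even per month, the relative fall is (1+km)^(−1−1/k) = 2^(−2) = 25%. It runs from 2.5^(−2) = 16% (m = 1.5, k = 1) to 1.3^(−3) = 46% (m = 0.6, k = 0.5). With m down to 0.5 and k up to 2, the range is 12% to 51%.

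**3. Precision of change from baseline.** Let B be the baseline count and F the 3-month count.
- E[rate] is the annual rate in step 2; E[rate²] = (1+k)m²[1 − (1+km)^(−1/k−2)]/s = 2(1 − 1/8)/0.5 = 3.5, so Var(rate) = 3.5 − 1.5² = 1.25.
- Var(F) = 0.375 + 1.25/16 = 0.453.
- E[B] = um/s; Var(B) = u²(1+k)m²/s + E[B] − E[B]² = 4 + 2 − 4 = 2 for 12 months.
- Cov(B,F) = (u/4)(1+k)m²/s − E[B]E[F] = 1 − 0.75 = 0.25.
- Mean scale: variance ratio (0.453 + 2 − 0.5)/0.453 = 4.31, so SE × 2.08.
- Log scale: (0.453/0.375² + 2/2² − 2·0.25/(0.375·2))/(0.453/0.375²) = (3.22 + 0.50 − 0.67)/3.22 = 0.95, so SE × 0.97.

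Over m = 0.6 to 1.5 and k = 0.5 to 1:

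| Baseline look-back | SE multiplier, mean scale | SE multiplier, log scale |
| --- | --- | --- |
| 12 months | 1.9–2.2 | 0.95–1.00 |
| 3 months | 1.3–1.5 | 1.17–1.23 |
| 1 month | 1.1–1.2 | 1.55–1.71 |

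With m down to 0.5 and k up to 2, the overall ranges are 1.02–2.34 and 0.87–1.71.

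**4. Baseline as covariate instead.** The correlation is 0.25/√(2 × 0.453) = 0.26, so the variance is multiplied by 1 − 0.26² = 0.93. Over the wider grid this factor is 0.75 to 1.00, so nothing is lost.

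**5. Counting from randomisation.** Exposure is 1/4 + 1/13 = 0.327 year, the mean is 0.490 and the variance is 0.490 + 0.327² × 1.25 = 0.624. The log-rate variance is proportional to 0.624/0.490² = 2.59, against 3.22 for the last 3 months only, a reduction of about 19%. Over m = 0.6 to 1.5 and k = 0.5 to 1 it is about 18% to 22%; with k = 2 it can be nearer 15%.

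**The case against.** The strongest reply is that the periods are inferred. The past-year rule is an eligibility criterion and not a recall window, a fixed window at each visit is possible, and Table 2 might give hospital use its own schedule. This stands. What the available text shows for certain is narrower: no period is stated and no exemption is made for this outcome.

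A reader might infer that every patient starts with a count of at least 1. That needs a look-back of about 12 months that includes the entry admission. With 1 to 3 months, only 11% to 49% of patients would have a baseline admission under the assumed rates. Emergency visits are not selected by the entry rule at all, and the term readmissions may already exclude the qualifying admission. Excluding it would not make the periods comparable, however: in the illustration the baseline becomes 2.00 − 1 = 1.00 per year against 1.5 afterwards.

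A reader might also infer that the treatment comparison is biased. It is not. Eligibility and baseline assessment precede allocation, so selection and period length act on both arms alike. The Objectives section frames a comparison between arms at 3 months and does not target a within-arm trend.

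Nor can one say that the contrast is noisier in every case. The protocol names no link, and means with SDs is only a descriptive summary. On a log scale with a 12-month look-back there is no loss. Equally, nothing says that the T6 count is limited to the last 3 months, so the gain in step 5 applies only if that was intended.

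Link and offset may fairly be left to an analysis plan. The counting period cannot, because it is part of the outcome definition and of the interview question.

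**Conclusion.** The point holds in a conditional form. As written, an event count with no stated period sits in a repeated-measures scheme built for scale scores, in a sample selected on a past admission. If the natural intervals and a long baseline look-back are used, a within-arm fall from baseline would be largely selection and period length: with no treatment effect, 16% to 46% per month from the entry rule alone under m = 0.6 to 1.5 and k = 0.5 to 1. The between-arm contrast stays unbiased. Its standard error as a change from baseline is about 1.1 to 2.2 times that of the follow-up count on the mean scale and 0.95 to 1.7 times on a log scale. All these sizes rest on assumed rates, heterogeneity and look-backs. This is one secondary outcome; the quality-of-life primaries and the sample size are untouched. It should be corrected, because a better definition costs little.

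**What to change.** In Health service utilization and Statistical analysis, take hospital use out of the baseline/post/3-month scheme. Define it as admissions and emergency visits, all-cause and cardiac-related, from randomisation to the 3-month assessment. Compare arms as one rate, with each patient's follow-up time as offset; this also handles intervals lengthened by suspended sessions. Record prior-year admissions, including the qualifying one, as a baseline covariate only and never as the time-zero value of the outcome. Align the general sentence in Outcomes, and Table 2 if it lists this outcome.

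The cost is wording in those sections and one interview question tied to the date of randomisation; no new data source is needed. The downside is that this outcome loses its separate post-intervention result, where few events are expected anyway: a mean of about 0.06 to 0.16 admissions per patient over 4 weeks under m = 0.6 to 1.5 and k = 0.5 to 1.

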**Primary outcomes**

The primary outcomes are the patients’ HRQOL and their FCs’ HRQOL. The patients’ HRQOL will be comprehensively evaluated by the CHF-specific HRQOL scale utilizing the short form of the Kansas City Cardiomyopathy Questionnaire (KCCQ) (70) and by generic HRQOL measures using the Five-dimensional five-level EuroQol (EQ-5D-5L) (58), while the FCs’ HRQOL will be evaluated only by using the EQ-5D-5L(58).

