**2 Methods**

**Objectives**

This study is proposed with the objective of evaluating the effectiveness of a dyad ACT-based intervention delivered via smartphone for CHF patients and their FCs compared with CHF education only at a 3-month follow-up on: (1) Patient and FC outcomes: HRQOL (primary outcome), perceived health status, anxiety, depressive symptoms; perceived quality of the relationship, psychological flexibility, self-compassion, and perspective-taking; (2) Patient-only outcomes: Hospital service utilization; CHF self-care behavior; and (3) Caregiver-only outcome: Caregiving burden.

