## A prior power analysis was performed to estimate the sample size needed in this study using G*Power. Previous studies in CHF have shown that mean differences in HRQOL between patients who received a psychosocial intervention and the usual care ranged from 0.11 to 0.68 (42). For ACT interventions targeting HRQOL, a recent review meta-analysis reported a mean effect of 0.48 for the clinical and non-clinical population, ranging from 0.37 to 1.55 when those who received the ACT intervention were compared to the active control, not including CBT (43). Thus, an estimated effect size of 0.50 was adopted across the above reviews. Targeting that effect size at a power of 0.8 with a prior power calculation, a minimal sample size of 128 is required to detect the difference between the ACT group and CE groups. Considering a weighted dropout rate of 16% for those participating in an ACT intervention indicated in a recent meta-analysis (44), and given group-setting and patient-caregiver dyadic participant requirements for the interventions, the total sample size was increased to 160 patient-FC dyads, accounting for an anticipated dropout rate of 20%.

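### Three primary HRQOL measures share one unadjusted two-sided 0.05 level with no success rule or named primary contrast, while the sample size gives 0.8 power for a single test

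*Protocol*

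**What the plan says.** Primary outcomes (Protocol): "The primary outcomes are the patients’ HRQOL and their FCs’ HRQOL". The patient's HRQOL is measured with the KCCQ short form and also with the EQ-5D-5L. For caregivers, "HRQOL will be evaluated only by using the EQ-5D-5L(58"). The instrument descriptions that follow give each a single score: a KCCQ overall score from 0 to 100 and an EQ-5D-5L utility. None of the three measures is ranked above the others.

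Timing: under Outcomes, effectiveness is assessed "at baseline, immediately post-intervention, and at 3 months post-intervention". Under Objectives, the intervention is "compared with CHF education only at a 3-month follow-up".

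Statistical analysis: "The differences in these outcomes between the ACT group and the CE groups over time will be analyzed using generalized estimating equations (GEE"). No interaction term, visit or contrast is singled out as the primary test. On the error level: "The level of statistical significance is predetermined at p<0.05 (two-tailed"). The section gives no testing order, no requirement that all measures succeed, and no adjustment.

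Sample size calculation: "an estimated effect size of 0.50 was adopted across the above reviews". With power 0.8 this leads to a minimum of 128, raised to 160 dyads for 20% dropout. The section does not say whose HRQOL, which instrument or which visit the calculation covers.

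**The concern.** The choice of primary measures, the significance level and the basis for power are all fixed in the Protocol, and they do not fit together. With three measures and no rule, two readings of a positive trial are open, and each breaks one of the stated properties:

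- If any one significant measure can be reported as the primary success, the chance of at least one false positive exceeds 5%.
- If all three must be significant, there is no inflation, but the chance of succeeding is below 0.8.

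The missing GEE contrast adds a second choice. The objective points to 3 months, but the analysis section does not carry that through to a named test. Unless both choices are settled before outcome data are seen, the result that is called primary can depend on the data.

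**Working it through.** **Inputs from the Protocol.** Three primary measures (Primary outcomes); two post-baseline assessments (Outcomes); 3 months named in Objectives; two-sided 0.05 (Statistical analysis); d = 0.50, power 0.8, N = 128, 20% dropout, 160 dyads (Sample size calculation); 1:1 allocation (Study design).

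**Assumed.** The correlations between test statistics, because the Protocol gives none. The power figures are for an unadjusted two-group comparison at one visit, as in the sample size section, and not for the GEE model.

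**1. The plan's own figure.** For a two-sample t-test with two-sided 0.05, d = 0.5 and power 0.80, the noncentral t gives 63.77, hence 64 per arm and N = 2 × 64 = 128. Power at 64 per arm is 0.801. Dropout: 128 / (1 − 0.20) = 160. Both figures reproduce exactly, as **one** test at two-sided 0.05.

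**2. Any one of three counts, at 3 months.**
- Independent tests: 1 − 0.95³ = 0.143.
- Equal correlation ρ, normal test statistics, c = 1.96: 1 − ∫ [Φ((c − √ρ z)/√(1−ρ)) − Φ((−c − √ρ z)/√(1−ρ))]³ φ(z) dz. This gives 0.125 at ρ = 0.5 and 0.098 at ρ = 0.8.

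**3. Worst case, both post-baseline visits tested separately (six tests).** Independent: 1 − 0.95⁶ = 0.265. With assumed positive correlation between measures (three structures, up to 0.8 for every pair) and 0.5 to 0.8 between visits, simulation gave about 0.15 to 0.23.

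**4. All three must succeed.** With d = 0.5 on every measure and 64 per arm, the normal test statistic is centred at 0.5 × √(64/2) = 2.83, so power per test is 0.807 by this approximation (0.801 by the t distribution).

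| Assumed correlation | Joint power for all three |
|---|---|
| 0 | 0.807³ = 0.53 |
| 0.5 | 0.62 |
| 0.8 | 0.70 |

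**5. Splitting alpha.** Bonferroni over three: 0.05 / 3 = 0.0167, which is also the first Holm step. Power per measure at 64 per arm and d = 0.5 is 0.656. Restoring 0.8 at that level would need 86 per arm, that is 172 evaluable dyads, or 172 / 0.80 = 215 with dropout.

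**The case against.** **Six tests.** A reader might infer from the two post-baseline assessments that six contrasts are each tested at 0.05, and that the chance of a false positive primary claim is therefore 14% to 26%. The documents do not support this. The assessment schedule is not a list of hypothesis tests, the analysis is described as a GEE comparison over time, and the objective names 3 months. Three tests is the supported family. What stands is that no contrast is named, so the six-test reading is not ruled out.

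**Independence.** The 14% figure is the independence case. Two HRQOL scales in one patient, and measures from two members of one dyad, are likely to be positively correlated, which lowers it. This objection stands: 14% is an upper figure, not the expected one. At an assumed correlation of 0.8 the error is still about twice the nominal 5%.

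**Two separate questions.** Patient and caregiver HRQOL could be seen as distinct questions in different people, each with its own 5%. Whether error control must span both is open to debate. Even then the patient question has two measures, with an error of 1 − 0.95² = 0.098 if independent, or about 0.08 at an assumed correlation of 0.7.

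**The stated 5% and 0.8.** A reader might infer that these figures are wrong. They are not: 0.05 is stated as a significance level with no familywise claim attached, and 0.8 is correct for the single comparison that the sample size describes. The gap is that neither describes a three-measure primary set.

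**The statistical analysis plan.** It is not shown and could supply a testing rule and a contrast. That is fair, and their absence alone would not be a finding. But the Protocol itself fixes three primary measures, one 0.05 level and a sample size for one test. A later alpha split would leave 160 dyads short of 0.8 power per measure at the split level.

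**Conclusion.** The point holds in a limited form. Three measures are primary, one unadjusted two-sided 0.05 level applies, and there is no hierarchy, success rule or named GEE contrast. N = 128 (160 with dropout) matches exactly one test.

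Its size depends on the rule that the Protocol does not state. If any one success counts, the familywise error at 3 months is at most 14%, and about 10% to 12.5% at assumed correlations of 0.8 to 0.5. It would reach 26% only if both visits were tested separately and all six tests were independent. If all three must succeed, there is no inflation, but joint power is about 0.53 to 0.70 at assumed correlations of 0 to 0.8, taking d = 0.5 on every measure and 64 evaluable dyads per arm. The power figures would differ somewhat under the planned GEE model.

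**What to change.** 1. Name the between-group GEE contrast at 3 months as the primary test for each measure, in line with the objective, and make the immediate post-intervention contrast secondary.
2. Control error over the three measures at two-sided 0.05, either by Holm or by a fixed sequence that stops at the first non-significant result. The Protocol ranks no measure and gives patient and caregiver HRQOL equal status, so the investigators should set the order before outcome data are seen. Putting the KCCQ first, as the disease-specific scale listed first, is one example.
3. State in the sample size section that the 0.8 power applies to a single test at two-sided 0.05. In a sequence that is the first measure. Under Holm, quote about 0.66 per measure at the first step (0.0167).

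This is a change of wording and needs no new data. A fixed sequence keeps 128/160 and the 0.8 power for its first test, but later measures cannot be claimed if an earlier one fails. Holm needs no ranking, but loses some power unless the sample is enlarged.
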